#### Coding

Coding will be completed manually, no auto-encoding will be carried out. The MedDRA coding dictionary will be used for medical terms reported as adverse events and cause of death, with the British National Formulary online used for concomitant medication data collected as part of adverse event reporting.

#### Data storage

Data stored on the trial database will be pseudonymised by linking to a unique participant ID number only. The name and any other identifying details will not be included in the trial data electronic file used for analysis or publication. A risk assessment for the trial database will be conducted, covering all the risks associated to the front-end and back-end security of the systems, outlined in the I’M WOMAN Database Development and Validation Plan. The LSHTM CTU Global Health Trials Group will provide an Investigator Site File (ISF) containing the essential trial documents, which the site must keep updated throughout the trial. Original copies of CRFs, consent forms, and source data will be kept securely at each participating site. These must be archived securely for 10 years after the overall end of the trial. Source documents include, but are not limited to, hospital records (from which medical history, previous and concurrent medication, clinical outcomes, and adverse events may be summarised onto CRFs), clinical and office logbooks, laboratory and pharmacy records, diaries, and correspondence. On all trial-specific documents other than the consent form, we will refer to the participant by their screening ID number and randomisation number. Study sites will provide data access to authorised representatives of the sponsor, the host institution, and regulatory authorities to allow trial-related monitoring, audits, and inspections.

#### Confidentiality {27}

The trial staff will ensure that participants’ confidentiality is maintained. Any identifiable data obtained by the LSHTM CTU Global Health Trials Group will be stored securely and confidentiality protected in accordance with relevant Data Protection regulations including the UK General Data Protection Regulation (GDPR) 2018. Participants will be identified only by a participant screening ID and randomisation number on all trial documents and any electronic database, except for the paper CRF which remains at participating sites, where participant initials may be added. All documents will be stored securely and only accessible by the trial staff and authorised personnel. The LSHTM CTU Global Health Trials Group will securely store copies of consent forms sent for monitoring, and these will be destroyed at trial closure. Only people authorised by the chief investigator, project lead, or trial manager will have access to the I’M WOMAN trial database. The trial database will be accessed through a complex password system which includes a password ageing mechanism (i.e. passwords will be changed every 90 days).

## Statistical methods

### Statistical methods for primary and secondary outcomes {20a}

We will draft a statistical analysis plan (SAP) for use by the Data Monitoring Committee (DMC) during their ongoing review. The SAP will be finalised before the trial database is locked for the final analysis.

The primary analysis comparing IM and IV tranexamic acid will be a per-protocol analysis. The analysis comparing tranexamic acid to placebo will be an intention-to-treat analysis. We will analyse the data and present statistics by randomised group. We will tabulate demographic and other baseline characteristics. Descriptive statistics for continuous variables will include the mean, standard deviation, median, range, and the number of observations. We will present categorical variables as numbers and percentages. Effect measures will be relative risk. Precision will be quantified using 95% confidence intervals. We will use the composite strategy to account for intercurrent events that may preclude the measurement of key efficacy and safety outcomes (e.g. early death, surgical interventions, discharge, or transfer to another hospital).

To compare the IV and IM routes of administration, we need to prespecify a non-inferiority margin—a predetermined margin of difference that is clinically acceptable. Women often experience treatment delays while waiting for a doctor or travelling to the hospital. Because tranexamic acid’s effectiveness falls by about 10% for every 15-min delay, a 1-h treatment delay corresponds to a 40% reduction in effectiveness. If IM administration preserves 60% of the benefit achieved with IV administration, IM tranexamic acid would be equivalent to an IV injection with a 1-h delay. An effect of this size from a more accessible route of administration with potentially fewer side effects would be clinically relevant. A 60% preservation fraction corresponds to a relative risk between IM and IV tranexamic acid of 1.13. If the upper limit of the two-sided 95% confidence interval for IM versus IV tranexamic acid is less than 1.13, then evidence of non-inferiority will have been provided.

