### Eligibility criteria {10}

For a woman to be eligible, the randomising clinician must be uncertain about whether to give tranexamic acid. If the clinician believes tranexamic acid is indicated based on the existing evidence, they should not randomise the woman into the trial. During the trial, if accumulating evidence from other trials clearly demonstrates that tranexamic acid prevents PPH with a favourable balance of benefits and harms, it would be unethical to randomise women to receive a placebo. If this happens, the placebo arm will be dropped, and we will continue to recruit women into the IM and IV TXA arms.

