#### Inclusion criteria

Women thought to be aged 18 years or older admitted to hospital for a vaginal or caesarean birth and who are known to have one or more risk factors for PPH will be potentially eligible. A list of major risk factors is provided in Additional file 8. If accumulating trial data or newly published research suggests that a particular factor is not strongly associated with an increased risk of PPH, we will focus on recruiting women with other/additional risk factors.

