#### Estimated event rate

In trials of tranexamic acid for PPH prevention, the event rate (a clinical diagnosis of PPH) varies from 8 to 15% depending on the mode of delivery [6, 7, 9]. We assumed an event rate of 11.5% in the placebo group, based on a roughly 50:50 ratio of vaginal to caesarean births.

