We will present baseline data, outcome data, and data on adverse events that might be associated with postpartum bleeding or tranexamic acid use to the DMC. We will use the Peto-Haybittle stopping rules, which require extreme differences to justify premature disclosure and involve an appropriate combination of mathematical stopping rules and scientific judgement, with the advantage that the exact number and timing of interim analyses need not be pre-specified. If there is a difference of at least three standard errors in favour of tranexamic acid compared to placebo, this will be taken as proof of a treatment benefit, and we will stop recruitment into the placebo group. The trial will continue to assess the non-inferiority of IM tranexamic acid compared to IV tranexamic acid. While early stopping based on evidence of non-inferiority is not recommended, early stopping based on inferiority is recommended to minimise patient exposure to an inferior intervention. The Peto-Haybittle stopping rule is appropriate as both the treatment and active control are the same drug given via different routes, with no good biological reason to expect the inferiority of the IM route. If there is a difference of at least three standard errors in favour of IV tranexamic acid compared to IM tranexamic acid, this will be taken as proof of inferiority, and we will stop recruitment into the IM tranexamic acid group.

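### The placebo arm can close mid-trial, but the tranexamic acid versus placebo comparison is not limited to women randomised while placebo was open

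*Protocol article*

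**What the plan says.** All references are to the protocol article.

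- **Closure on outside evidence.** Under Eligibility criteria {10}, if other trials clearly show benefit, "the placebo arm will be dropped, and we will continue to recruit women into the IM and IV TXA arms".
- **Closure on the trial's own data.** Under Interim analyses {21b}, a difference of at least three standard errors favouring tranexamic acid over placebo means that "we will stop recruitment into the placebo group. The trial will continue to assess the non-inferiority of IM tranexamic acid".
- **Analysis.** Under Statistical methods {20a}: "The analysis comparing tranexamic acid to placebo will be an intention-to-treat analysis. We will analyse the data and present statistics by randomised group". The effect measure is the relative risk with a 95% confidence interval.
- **Possible change in case mix.** Under Inclusion criteria, if a factor proves weakly related to PPH, "we will focus on recruiting women with other/additional risk factors".
- **Event rates.** Under Estimated event rate: "We assumed an event rate of 11.5% in the placebo group, based on a roughly 50:50 ratio of vaginal to caesarean births". The same section puts the rate between 8% and 15% depending on mode of delivery.

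No section limits the placebo comparison to women enrolled while placebo was available, or stratifies or adjusts it by recruitment period.

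**The concern.** A woman enrolled after placebo closes had no chance of receiving placebo. If she is counted in the tranexamic acid group against placebo women who were all enrolled earlier, randomisation does not support that part of the contrast. Any change in underlying PPH risk between the two periods then enters the relative risk as if it were a treatment effect. The article makes such a change foreseeable: it allows recruitment to move between risk factors, and it reports event rates that nearly double across modes of delivery.

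What is at stake depends on why placebo closed. Under the three-standard-error rule, the decision rests on concurrent data, so the damage falls on the final estimate and interval. If outside evidence prompted the closure, the trial may not yet have made its own placebo comparison, so the final test is exposed too.

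**Working it through.** **The plan's own figure first.** Inputs from Sample size {14} and Statistical methods {20a}: 30,000 women, 11.5% on placebo, relative risk 0.75 (8.625% on tranexamic acid), margin 1.13, two-sided 5% for superiority and one-sided 2.5% for non-inferiority. The allocation ratio is called optimal but not given. Taking joint power as superiority power times non-inferiority power, the best value is 0.872 with margin 1.13, or 0.886 with the unrounded margin 0.85/0.75. It occurs at about 2,400 placebo women, near 6:6:1 (IM:IV:placebo). This agrees with the stated power of just under 90%, so no stated figure is wrong. The point concerns the analysis set.

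**When the interim rule might act.** Let *a* be the placebo share. On the log relative risk scale, the fraction of recruitment at which the expected difference reaches three standard errors is

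f = 9 × [0.885/(0.115 × 30,000a) + 0.91375/(0.08625 × 30,000(1−a))] / (ln 0.75)².

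At 1:1:1 this is 9 × (0.000770 + 0.000530)/0.08276 = 0.14. It is 0.19 at 2:2:1, 0.40 at 6:6:1 and 0.57 at 9:9:1.

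**Drift (assumed).** Take 8% and 15% as the risks for the two modes of delivery. If the mix moves from 50:50 to 70:30 after closure, later control risk is 0.7 × 8 + 0.3 × 15 = 10.1%, or 0.3 × 8 + 0.7 × 15 = 12.9%.

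**Pooled estimate.** With T1 and T2 tranexamic acid women before and after closure and later control risk p2,

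expected pooled relative risk = RR × (T1 × 0.115 + T2 × p2) / [(T1 + T2) × 0.115].

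Worked example: 2:2:1 with closure at 20% gives 1,200 placebo women, T1 = 4,800 and T2 = 24,000.

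- True 0.75, p2 = 10.1%: (4,800 × 0.08625 + 24,000 × 0.75 × 0.101)/28,800 = 2,232/28,800 = 0.0775, and 0.0775/0.115 = 0.674.
- True 0.75, p2 = 12.9%: 2,736/28,800 = 0.0950, and 0.0950/0.115 = 0.826.
- No effect, p2 = 10.1%: (552 + 2,424)/28,800 = 0.1033, relative risk 0.899. The standard error of the log is √(0.8967/2,976 + 0.885/138) = 0.082, and ln 0.899/0.082 = −1.31. The two-sided 5% test rejects 25.7% of the time. With p2 = 12.9% the relative risk is 1.101 and rejection is 22.0%.

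The same formulas for three assumed scenarios (paired values are for p2 = 10.1% / 12.9%):

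| Ratio, closure | Placebo; T1; T2 | Estimate when true RR is 0.75 | 95% interval coverage | Rejection under no effect |
|---|---|---|---|---|
| 2:2:1, 20% | 1,200; 4,800; 24,000 | 0.674 / 0.826 | 75% / 78% | 25.7% / 22.0% |
| 6:6:1, 40% | 923; 11,077; 18,000 | 0.693 / 0.806 | 87% / 88% | 13.5% / 12.3% |
| 1:1:1, 50% | 5,000; 10,000; 15,000 | 0.695 / 0.805 | 60% / 64% | 41.8% / 37.9% |

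With p2 = 11.5% (no drift), the pooled estimate is 0.75 and rejection under no effect is 5% in every row.

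**The case against.** **The article does not say that later women are pooled.** A reader might infer that the plan has decided to compare them with earlier controls. It has not. The sentences under {20a} choose intention-to-treat for this contrast and say that results are shown by arm. Limiting the comparison to concurrent women is compatible with intention-to-treat, and a SAP not shown here may do so. This stands as a limit on the wording. It does not dispose of the point, because the article states both the adaptation and the analysis, and an analyst following both literally would pool. It also lets the SAP be finalised as late as just before database lock, which could be after closure.

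**There is an adjusted analysis.** Section {20b} plans adjustment for predicted baseline risk, and planned route of birth is collected at entry. In the route-mix illustration, the subgroup analysis by route would stay unbiased, and adjustment including route would remove much of the bias. But the adjusted analysis is additional, is aimed at chance imbalance, and names no recruitment period. Drift from causes not captured at baseline would remain.

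**Wider readings fail.** A reader might think that the non-inferiority result or a preserved-effect estimate is compromised. Non-inferiority is a direct IM versus IV test against a fixed 1.13, which stays concurrent after placebo closes, and no preservation estimate is planned. The stated adverse-event objective is also IM versus IV.

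**Closure is not shown to be likely.** The fractions of 14% to 57% depend on the unstated ratio and assume that the true relative risk is 0.75. Looks are not scheduled, and disclosure also requires an expected change in prescribing. No section plans the 70:30 shift. The no-effect case supposes that tranexamic acid does nothing in this trial although outside evidence has shown clear benefit, so it marks an extreme.

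**Conclusion.** The point holds as a conditional gap that should be closed before any arm is dropped. The article provides for early placebo closure with continued IM and IV recruitment, and it specifies the placebo comparison without a concurrency limit or period stratification. Harm needs both early closure and drift in PPH risk. Under the assumed scenarios (ratios from 6:6:1 to 1:1:1, closure at 20% to 50%, later control risk 10.1% or 12.9%), a true relative risk of 0.75 is estimated as about 0.67 to 0.70 or 0.80 to 0.83, and rejection under no effect is about 12% to 42%. Ratio, closure time and drift are all assumptions. The conclusion covers the final estimate and interval for tranexamic acid versus placebo, plus the final test when outside evidence caused the closure. It does not extend to the interim decision or to IM versus IV after placebo closes.

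**What to change.** State in the protocol or SAP, before any arm closes:

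- The primary tranexamic acid versus placebo analysis, and any secondary, safety or subgroup comparison with placebo, uses only women randomised while the placebo arm was open at their site. Treatment packs are held in stock at sites, so the closing date should be recorded for each site.
- Women randomised after that date enter a placebo comparison only in a sensitivity analysis adjusted for period.
- IM versus IV uses all women randomised while both arms were open, stratified by period (before and after the change in allocation). This wording also covers closure of the IM arm, which {21b} allows.

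This removes the bias from drift. It does not address the separate tendency of estimates to be exaggerated after stopping at a boundary.

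**Cost.** The restricted comparison has roughly 5% to 30% more variance in the log relative risk, least when the placebo arm is small, because placebo numbers dominate the variance. With a true relative risk of 0.75 and no drift, the increase is about 7% (6:6:1, 40%), 27% (2:2:1, 20%) and 32% (1:1:1, 50%: standard error 0.0443 to 0.0510). Very early closure with equal allocation would cost more: at 1:1:1 and 14%, the standard error goes from 0.0766 to 0.0963, and (0.0963/0.0766)² = 1.58. If placebo closed at 50%, superiority power from concurrent women would still exceed 99% at 1:1:1 and 2:2:1, and be about 95% at 5:5:1 and 80% at 9:9:1.

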### Interim analyses {21b}

The DMC is responsible for deciding whether to reveal the unblinded results (overall or for a particular subgroup) to the Trial Steering Committee (TSC) while the trial is underway. The DMC will do this only if two conditions are satisfied: (1) the results provide proof beyond reasonable doubt that treatment is either definitely harmful/inferior or definitely favourable for all or for a particular subgroup in terms of a major outcome and (2) the results are expected to substantially change the prescribing patterns of clinicians who are familiar with other existing trial results. The exact criteria for ‘proof beyond reasonable doubt’ are not and cannot be specified by a purely mathematical stopping rule but are strongly influenced by such rules. The DMC Charter will refer to the Peto-Haybittle stopping rule, whereby an interim analysis of a major outcome must involve a difference between the treatment and control of at least three standard errors to justify premature disclosure [33, 34]. An interim subgroup analysis would have to be even more extreme to justify disclosure.

We will present baseline data, outcome data, and data on adverse events that might be associated with postpartum bleeding or tranexamic acid use to the DMC. We will use the Peto-Haybittle stopping rules, which require extreme differences to justify premature disclosure and involve an appropriate combination of mathematical stopping rules and scientific judgement, with the advantage that the exact number and timing of interim analyses need not be pre-specified. If there is a difference of at least three standard errors in favour of tranexamic acid compared to placebo, this will be taken as proof of a treatment benefit, and we will stop recruitment into the placebo group. The trial will continue to assess the non-inferiority of IM tranexamic acid compared to IV tranexamic acid. While early stopping based on evidence of non-inferiority is not recommended, early stopping based on inferiority is recommended to minimise patient exposure to an inferior intervention. The Peto-Haybittle stopping rule is appropriate as both the treatment and active control are the same drug given via different routes, with no good biological reason to expect the inferiority of the IM route. If there is a difference of at least three standard errors in favour of IV tranexamic acid compared to IM tranexamic acid, this will be taken as proof of inferiority, and we will stop recruitment into the IM tranexamic acid group.

### Methods for additional analyses (e.g. subgroup analyses) {20b}

In a large trial such as I’M WOMAN, baseline characteristics of participants that may influence the outcome should be evenly distributed between the treatment and placebo groups, so that any difference in outcome can be attributed to the intervention. However, it is still possible that a chance imbalance in important prognostic factors could influence the results. To investigate this possibility, an analysis adjusted for baseline risk will be conducted. A prognostic model will be built based on pre-specified baseline variables and used to estimate the predicted risk of the outcome at baseline.

Planned subgroup analyses will be conducted on the primary outcome comparing tranexamic acid to placebo. Subgroup variables include severity of anaemia (no anaemia vs mild anaemia vs moderate/severe anaemia) and route of birth (vaginal vs caesarean). We will explore potential confounding in subgroup analyses. Randomisation creates treatment groups that are balanced; however, the strata of subgroups may not be balanced [35]. It is possible that some baseline variables will be associated with the subgroup variable and the treatment effect. We will investigate the association of anaemia and route of birth with other baseline variables and adjust for any potential confounders as necessary. We will report relative risks (RR) and confidence intervals alongside *p*-values from tests for interaction. Unless there is strong evidence of interaction (*p* < 0.001), we will take the overall RR as the most reliable estimate of the RR in all subgroups.

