#### Size of the treatment effect

Based on the existing evidence in PPH prevention and surgical trials, we assumed a 25% reduction in PPH with tranexamic acid (RR = 0.75).

A trial of about 30,000 women has almost 90% power to detect that (1) tranexamic acid is more effective than placebo and (2) IM tranexamic acid is at least 60% as effective as IV tranexamic acid. We assumed a two-sided type 1 error rate of 5% for the superiority arm and a one-sided rate of 2.5% for the non-inferiority arm. Our sample size and power calculations were made using methods described by Stucke and Kieser (2012) [32]. We confirmed our results using simulation. An optimal allocation ratio was used to maximise study power with patients allocated to receive IM tranexamic acid, IV tranexamic acid and placebo.

Because the true event rate and treatment effect are unknown, we will re-estimate the sample size if unplanned interim analyses indicate a lower-than-expected event rate or if new information emerges which changes beliefs about the expected treatment effect.

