### Data collection and management

#### Plans for assessment and collection of outcomes {18a}

The local trial staff will collect consent, baseline, outcome, and adverse event data and send them to the LSHTM CTU Global Health Trials Group by entering them into the online trial database. All staff authorised to collect trial data will be trained in data collection procedures and GCP. The staff will first enter trial data onto paper case report forms (CRF) and then the trial database to allow easier data control. After completing the consent procedure, an entry form will be used to collect baseline data including the woman’s age, gestational age, parity, recent Hb or PCV if known, multiple pregnancy, planned route of birth, previous PPH, hypertensive disease, placental abnormality, antepartum haemorrhage, and any other PPH risk factors. We will also collect the date and time of randomisation and IM injection sites. We will follow up participants until discharge, death, or the end of the postnatal period (42 days), whichever occurs first, and trained staff will record outcome data onto an outcome form.

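### Baseline adjustment is planned only as a check on chance imbalance; making it the primary estimate would add a little precision to the IM versus IV test at almost no cost

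*Protocol article*

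**What the plan says.** The section on additional analyses {20b} expects baseline characteristics to be balanced in a trial of this size, but allows that a chance imbalance could influence the results. To look into that possibility, it says that "an analysis adjusted for baseline risk will be conducted". On method it says: "A prognostic model will be built based on pre-specified baseline variables". Its remark on balance refers to the treatment and placebo groups, so it is not explicit that the adjusted analysis also covers IM versus IV.

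The section on primary and secondary outcomes {20a} makes the IM versus IV comparison per-protocol and the comparison with placebo intention-to-treat. It states: "Effect measures will be relative risk". Precision is given by 95% confidence intervals and no covariate is named. The decision rule compares the upper limit for IM versus IV with a fixed margin: "A 60% preservation fraction corresponds to a relative risk between IM and IV tranexamic acid of 1.13".

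The data for adjustment are already collected. The entry form {18a} records age, gestational age, parity, multiple pregnancy and planned route of birth, together with "previous PPH, hypertensive disease, placental abnormality, antepartum haemorrhage, and any other PPH risk factors". Recent haemoglobin or packed cell volume is recorded only where known, and section {20c} rules out imputation.

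**The concern.** Adjustment for prognostic baseline variables does more than correct imbalance. It removes outcome variance even when the arms are perfectly balanced. Non-inferiority here turns on one upper confidence limit, so any narrowing of that interval bears directly on the decision. The trial collects the covariates and plans the prognostic model, but uses the model only where it cannot affect the conclusion.

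The claim of even balance also rests on randomisation, and it applies less fully to the per-protocol set in which the 1.13 margin is tested.

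For a marginal relative risk the alternative has no conceptual price. Standardising model predictions over the trial population targets the same quantity as the unadjusted ratio, so the margin keeps its meaning.

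**Working it through.** **Inputs from the protocol article**
- Total of about 30,000 women, with power of almost 90% for both aims (Size of the treatment effect).
- Placebo event rate 11.5%, at a roughly 50:50 mix of vaginal and caesarean births (Estimated event rate).
- Relative risk with tranexamic acid 0.75, so 0.115 × 0.75 = 8.625% in each active arm.
- Non-inferiority error rate: "a one-sided rate of 2.5% for the non-inferiority arm".
- The event rate in earlier trials "varies from 8 to 15% depending on the mode of delivery".

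**Assumptions**
- True IM/IV relative risk is 1.
- The allocation ratio is called optimal but no figure is given, so ratios of the form k:k:1 were searched.
- Adjustment multiplies the variance of the marginal relative risk by (1 − R²), where R² is the share of outcome variance explained by the covariates.

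**Step 1. The margin.** Preserving 60% of a 25% reduction leaves a 15% reduction with IM. The ratio is 0.85/0.75 = 1.1333, which the article rounds to 1.13.

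**Step 2. The stated power, unadjusted.** SE of the log relative risk = √[((1 − p)/p) × (1/n_IM + 1/n_IV)] and power = Φ(ln(margin)/SE − 1.96). At 6:6:1 each active arm has 13,846 women and the placebo arm 2,308. SE = √[(0.91375/0.08625) × (2/13,846)] = 0.0391.
- Margin 1.13: Φ(0.1222/0.0391 − 1.96) = 87.8%.
- Margin 1.1333: 89.2%.
- Superiority, pooled tranexamic acid versus placebo: 99.3%.
- Joint power as a product, margin 1.1333: 0.892 × 0.993 = 88.6%, the highest value in the search.

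The stated figure is therefore reproduced with no adjustment.

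**Step 3. What route of birth explains.** R² = 0.25 × (difference in risk)² / [p(1 − p)].
- At placebo rates: 0.25 × 0.07² / (0.115 × 0.885) = 1.2%.
- At active-arm rates (6% and 11.25%): 0.25 × 0.0525² / (0.08625 × 0.91375) = 0.9%.

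This is the only covariate whose strength can be computed from the article. It treats the planned route on the entry form as equal to the mode of delivery.

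**Step 4. Gain at 6:6:1**

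| R² | SE | Upper 95% limit if observed RR = 1.00 | Power, margin 1.13 | Power, margin 1.1333 |
|---|---|---|---|---|
| 0 | 0.0391 | 1.080 | 87.8% | 89.2% |
| 1.2% (route of birth) | 0.0389 | 1.079 | 88.2% | 89.6% |
| 5% (assumed) | 0.0381 | 1.078 | 89.4% | 90.7% |
| 10% (assumed) | 0.0371 | — | 90.9% | 92.1% |

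In sample-size terms, R² of 1.2% is worth 0.012 × 30,000 = 360 women, and R² of 5% is worth 1,500. If individual risks are logit-normal with mean 8.6% (a further assumption), R² of 4% and 7% correspond to c-statistics of about 0.69 and 0.73, so 5% lies between them.

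**Step 5. When the gain is lost.** Dropping a fraction f of women inflates the variance by 1/(1 − f), which cancels the factor (1 − R²) when f = R². A complete-case model that lost a little over 1% of women to unknown haemoglobin would use up the whole gain from route of birth.

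**The case against.** The strongest reply is that nothing here is wrong. An unadjusted relative risk in about 30,000 randomised women is valid, a prespecified adjusted analysis supports it, and the covariates of a primary model are normally settled in the analysis plan, which is not shown. The article never says outright that the primary estimate is unadjusted. It also ties the decision to the main interval, so a conflict between the two estimates is largely resolved already. Most of this stands, and it makes the point an improvement and not a correction. It does not remove the point, because the article does state a role for adjustment, and that role makes sense only if the main estimates are unadjusted.

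A reader might infer more than the documents support:
- **That the non-inferiority test needs this precision.** At 1:1:1 or 2:2:1 the power at margin 1.13 would be 75.7% or 82.9%. The article states neither ratio, and neither reproduces its power figure. The article does admit that the true event rate is unknown and may be lower than expected, so spare precision has some value.
- **That the collected risk factors are strong predictors.** The article gives no strength for any of them except mode of delivery. Every participant already has at least one risk factor, which may narrow the spread of baseline risk.
- **That the gain is wholly free.** That holds only if women with unknown haemoglobin stay in the model.

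**Conclusion.** The point holds as a minor, optional improvement. The gain in non-inferiority power is about 0.4 points on the article's own figures (slightly less at the active-arm R² of 0.9%). It is about 1.5 points if the full model reached an assumed R² of 5%. For the comparison with placebo, power at 6:6:1 is already above 99%, so the benefit there is only a slightly narrower interval.

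These sizes rest on equal true efficacy of the two routes, an allocation near 6:6:1 inferred from the stated power, and the (1 − R²) approximation. Calling the present plan invalid or underpowered would go beyond what the documents show.

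**What to change.** In the analysis plan, for both IM versus IV and tranexamic acid versus placebo:
- Make the primary estimate the marginal relative risk, standardised from a model with treatment, planned route of birth and other prespecified baseline predictors recorded at entry.
- Give haemoglobin or packed cell volume an unknown category, so that no woman is dropped.
- Keep the 1.13 margin.
- Report the unadjusted relative risk as supportive, and state in advance that the adjusted estimate decides.

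This needs no new data and no more women. The cost is slightly more analysis work and the discipline of fixing the covariates before unblinding. The article has the plan finalised before database lock, so there is room to do this.
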